### Treatment assignment and randomization

Households will be randomized as clusters to receive either IFN ß-1a treatment or standard of care, once a household meets all the inclusion and none of the exclusion criteria. Households will be randomized to IFN ß-1a treatment or standard of care at a 1:1 ratio. The minimization technique (biased coin, *p* = 0.7) will be applied to achieve balance between groups stratified by the total number of people within the household. This will be implemented through a platform provided by the Telethon Kids Institute (https://qminim.telethonkids.org.au/).

Households will be randomized during the first home visit, once eligibility is confirmed, participants have signed informed consent, and baseline data collection procedures are completed. Field team members will contact the research laboratory, at which time the household assignment to treatment or standard of care will be made by the randomization software. Participants and study staff will not be blinded to randomization of treatment or standard of care, but all data analyses will be blinded to allocation.

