### Control arm

Participants randomized to the control group will receive standard of care, including symptom-based supportive treatment provided by the individual’s personal medical provider. This could include acetaminophen, non-steroidal anti-inflammatory drugs, cough suppressants, antibiotics, inhaled bronchodilators. Participants in this arm will not receive any IFN ß-1a treatment or a placebo. This standard of care approach was selected as the comparator, since no other approved intervention medications are available for non-hospitalized cases.

All participants, regardless of their allocation group, will receive a brochure with the recommendations of the Chilean Government for patients with COVID-19, including household isolation. Within each household, the index case will be asked to isolate from their contacts.

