All adverse events/serious adverse events will have their relationship to the trial intervention and severity assessed by the investigator who evaluates the adverse event, based on temporal relationship and his/her clinical judgment. All severe adverse events will be reported immediately to the sponsor, except for those SAEs that are identified as not requiring immediate reporting. The immediate reports should be followed promptly by detailed, written reports. Clinic trial liability insurance will cover costs for participants who suffer harm during trial participation. Investigators will ensure harmed participants receive treatment for their condition.

IFN treatment is known to induce injection site erythema and, in up to 80% of recipients, an ‘influenza like’ syndrome, comprising fever, headache and body aches. Importantly, there are no respiratory signs or symptoms associated with IFN treatment, i.e. the response to IFN treatment is different than COVID-19 disease. However, ‘flu-like symptoms’ also occur in COVID-19 disease, and could lead to an increase in clinical tests in the IFN treated cohort if not appropriately managed. There are several strategies that may mitigate this potential response to IFN treatment that already constitute standard practice for multiple sclerosis (MS) patients on IFN therapy. Participants will be informed about the likely side effects of IFN treatment and asked to monitor and manage these. Monitoring consists of self-assessment of symptoms (there are no respiratory symptoms or anosmia known to be associated with IFN use) and the time frame during which this ‘influenza like’ syndrome following IFN treatment occurs (restricted to the first 4–24 h after administration of an IFN dose). Management consists of advising the participant to take acetaminnophen (provided to the participant) from the time of IFN administration up to 24 h after, to reduce the likelihood of this ‘influenza like’ syndrome. This approach is recommended for individuals with MS receiving IFN therapy (see PLEGRIDY package insert product monograph) and reduces syndrome symptoms by 80%.

Interferon ß-1a is safe when taken during pregnancy, with no evidence of increased rates of congenital anomalies or spontaneous abortions, according to data reported by the European IFNbeta Pregnancy Registry. If a female subject is diagnosed as pregnant by a positive.

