### Data analyses

Analyses of data for primary and secondary objectives will be conducted per protocol and through intent-to-treat using the procedures detailed below and described in greater detail in a statistical analysis plan, available upon request. Data analysts will be blind to treatment allocation. Analyses will be conducted using R and statistical coding will be available to the public upon request and approval by the investigators.

#### Analysis for primary objective 1

The Primary Objective 1 is to determine whether IFNß-1a treatment reduces the number of COVID-19 cases still shedding SARS-COV-2 in saliva at day 11 following randomization. Statistical analysis of SARS-CoV-2 RT-PCR results from the index case population will be undertaken comparing IFN ß-1a treated index cases to index cases receiving only standard of care. A linear regression model (binomial family, logit link for dichotomous outcomes) will be applied to data collected, where a risk ratio (and 95% confidence interval) will be reported for the treatment arm variable, adjusted for age, sex, baseline viral load and vaccination status at enrollment.

#### Analysis for primary objective 2

The Primary Objective 2 is to determine whether IFN ß-1a treatment reduces the incidence of SARS-CoV-2 transmission from an index case to treatment-eligible household contacts, as measured by upper airway RT-PCR in contacts at day 11 after randomization. Statistical analysis of SARS-CoV-2 RT-PCR results from household contacts will be undertaken comparing households assigned to IFN ß-1a treatment or standard of care. A linear regression model (binomial family, logit link for dichotomous outcomes) with clustering within a household will be applied, where a risk ratio (and 95% confidence interval) will be reported for the treatment arm variable, adjusted for age, sex, baseline viral load of the index case, vaccination status of the index case, vaccination status of eligible contacts, contacts between index case and household contacts during the initial 11-day period, baseline RT-PCR and antibody levels of treatment eligible contacts at enrollment, number of household members and physical details of the household size, e.g. number of bathrooms, number of bedrooms.

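### The objective 2 model adjusts for index–contact exposure over days 1–11, a post-randomisation variable that can bias the treatment effect if allocation changes behaviour

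*Protocol article*

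**What the plan says.** In the protocol article, the analysis of primary objective 2 compares infection among household contacts between arms, "as measured by upper airway RT-PCR in contacts at day 11 after randomization". A binomial regression "with clustering within a household will be applied, where a risk ratio (and 95% confidence interval) will be reported for the treatment arm variable"; the model carries a list of covariates. One of them is "contacts between index case and household contacts during the initial 11-day period". Nothing in that section confines this covariate to a sensitivity or mediation analysis. Analyses are to be both per protocol and intention to treat.

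Timing and blinding are set out under Treatment assignment and randomization: "Households will be randomized during the first home visit, once eligibility is confirmed", after baseline data collection, and "Participants and study staff will not be blinded to randomization of treatment or standard of care". Only the analysts are blind. Under Control arm: "Participants in this arm will not receive any IFN ß-1a treatment or a placebo". Advice on isolation is common to both arms; in each household "the index case will be asked to isolate from their contacts". Under Data and safety monitoring, interferon is expected to cause, "in up to 80% of recipients, an ‘influenza like’ syndrome, comprising fever, headache and body aches".

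**The concern.** Contact over days 1–11 is behaviour that occurs after the household knows its allocation. An injection reaction could lead a participant to keep apart; a sense of being protected could do the reverse. Adjusting for a variable that allocation has changed does two things:

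- It removes from the arm effect whatever acts through behaviour.
- It makes the arms differ on unmeasured causes of both contact and infection, such as caregiving or household closeness, because contact is then a common effect of arm and those causes (a collider).

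At stake is the meaning of a co-primary estimate. The objective asks whether treatment reduces transmission, and the plan commits to intention to treat. A ratio conditional on post-randomisation contact need not answer that question, nor is it a clean biological effect.

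**Working it through.** **Plan's own figures.** The article gives no figure for contact by arm or for the effect of contact on infection, so there is nothing to reproduce on this point. The stated power for objective 2 does not bear on it.

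**Timing.** Randomisation: day 1. Covariate window: the initial 11 days. Outcome: day 11. The covariate spans the whole outcome window.

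**Assumed inputs (illustrative).** Close contact in 50% of controls; contact triples the odds of infection; log-odds of infection without contact a = ln(0.2/0.8) − 0.5·ln 3 = −1.936. Hence:

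- Control risk without contact: 1/(1+e^1.936) = 0.126
- Control risk with contact: 1/(1+e^0.837) = 0.302
- Overall control risk: 0.5×0.126 + 0.5×0.302 = 0.214

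**Step 1: no direct drug effect, arm shifts contact by 20 points.**

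- Contact 30% on IFN: risk 0.7×0.126 + 0.3×0.302 = 0.179; OR (0.179/0.821)/(0.214/0.786) = 0.80.
- Contact 70% on IFN: risk 0.3×0.126 + 0.7×0.302 = 0.249; OR 1.22.
- Adjusted for contact, the OR is 1.00 in both cases. The effect of assignment disappears from the estimate.

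**Step 2: direct OR 0.5 (the article's design value).** Halving the odds gives IFN-arm risks of 0.0673 without contact and 0.178 with contact. The adjusted RR is standardised over the pooled contact distribution.

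| Contact on IFN | IFN risk | Total-effect RR | Contact-adjusted RR |
|---|---|---|---|
| 67% | 0.333×0.0673 + 0.667×0.178 = 0.141 | 0.141/0.214 = 0.66 | 0.132/0.229 = 0.58 |
| 50% | 0.5×0.0673 + 0.5×0.178 = 0.123 | 0.57 | 0.57 |
| 33% | 0.667×0.0673 + 0.333×0.178 = 0.104 | 0.49 | 0.113/0.199 = 0.57 |

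For the first row, pooled contact is (0.50+0.667)/2 = 0.583, so the adjusted risks are 0.417×0.0673 + 0.583×0.178 = 0.132 and 0.417×0.126 + 0.583×0.302 = 0.229. For the third row, pooled contact is 0.417. A simulation of 1.5 million contacts agrees within 0.01. Adding an unmeasured factor that doubles the odds of both contact and infection per SD, the simulated RR goes from 0.69 to 0.59, or from 0.53 to 0.64. The shift is about 0.08 to 0.10 either way.

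**Step 3: shared unmeasured cause, no direct drug effect.** A standard-normal factor adds 1 per SD to the log-odds of both contact and infection, and the arm shifts contact by about 16 points.

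- If contact itself has no effect on infection, a true OR of 1.00 becomes 1.13 (contact lower on IFN) or 0.89 (contact higher).
- If contact triples the odds, the true total effect is OR 0.86 or about 1.14, and the adjusted OR is 1.13 or about 0.9. Adjustment reverses the direction.

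**Step 4: arm does not shift contact.** With no drug effect, the adjusted and unadjusted ORs are both 1.00, even with the shared cause. With a direct OR of 0.5 and the shared cause, the RR is 0.61 both ways.

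These calculations concern the point estimate in large samples and ignore household clustering.

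**The case against.** The strongest reply is that nothing in the article shows that allocation changes contact. The flu-like syndrome is confined to 4–24 hours after a dose and is treated with acetaminophen, said to reduce symptoms by 80%; controls are told to take acetaminophen too. Day 11 saliva is taken just before the third dose, so only the day 1 and day 6 doses can act before the endpoint. Both arms get the same isolation advice. A 16- to 20-point shift in contact by this route is undocumented, and the sense-of-protection route is conjecture. This stands against any claim about size. It does not justify building an assumption of no shift into a co-primary model.

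Second, Fisher's exact and stratified Cochran-Mantel-Haenszel tests are planned for both primary objectives, and the sample size for objective 2 rests on the latter. The article does not say that they use 11-day contact. It presents them as additional analyses, however, so they mitigate the problem without curing it.

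Third, contact is prognostic and adjustment may add precision. That is true, but precision can be sought from baseline covariates without this risk. Blinding the analysts does not help, since the variable comes from participants' own behaviour.

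A reader might infer more than the text supports in three places:

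- *That the adjustment necessarily biases the effect or breaks the randomised comparison.* Step 4 shows that it need not.
- *That every other covariate is fixed at baseline.* Vaccination status is dated at enrolment for objective 1 but undated in the objective 2 list.
- *That infected contacts withdrawing is enough on its own.* If infection reduces contact equally in both arms, the log-odds of infection given arm and contact are those given arm plus a term in contact alone, so the arm OR does not move. The case rests on allocation changing contact.

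**Conclusion.** The point holds in conditional form. The article places a post-randomisation variable, measured over the outcome window, in the primary model of a co-primary objective in an open-label trial without placebo. If allocation or knowledge of it alters contact, the reported ratio is not the intention-to-treat effect and can err in either direction. Under the assumptions above, the risk ratio shifts by about 0.08 to 0.10 when the direct OR is 0.5, and benefit remains benefit in those cases; with no direct effect, the direction can reverse. If contact does not differ by arm, the estimate is essentially unchanged. Confidence is high that the flaw is present; its size and direction cannot be known from the article. It should be corrected before any analysis by arm, because it bears on how a co-primary result is read.

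**What to change.** Delete the 11-day contact variable from the primary model for objective 2. Keep only covariates measured at or before randomisation, and date vaccination status of index cases and contacts at enrolment, as objective 1 already does. Report 11-day contact by arm descriptively, and use it only in an analysis labelled exploratory or mediation.

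Adjust for pre-randomisation contact only if it was already collected. The day 1 procedures in Table 2 list no such item, and 251 of the 310 planned households were enrolled at manuscript submission, so that replacement cannot be assumed to be free.

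The deletion costs one line of wording and no data. The downside is some possible loss of precision from dropping a prognostic variable.

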#### Secondary analyses

Additional analysis of both primary objectives will be conducted to include more rigorous group comparisons, e.g. Fisher’s exact test of proportions and a stratified Cochran-Mantel–Haenszel test of proportions. If the primary analysis method, the generalized linear model with binomial family and log link, does not fit the data well, or converge, a logit link will be used, meaning an adjusted odds ratio and 95% confidence interval will be reported. Specifically, a regression model will be used where the outcome variable is Yes/No for SARS-CoV-2 from the day 11 saliva specimen, with odds ratio and 95% confidence interval reported treatment (active/control) variable, following covariate adjustments. Primary objective 2 analysis will include clustering within households, where appropriate. Secondary outcomes will be reported and analyzed as above for the primary outcomes. Poisson and/or ordinal regression analysis will be conducted to compare days of viral shedding between the IFN treated and standard of care groups. The Cox proportional hazards regression model, with similar adjustments for variables as above, will be employed to examine time based, and specifically time-censored, outcome variables between groups. In addition, Bayesian analyses will be estimated using data-generated distributions of viral shedding at days 11, 16, and 29, and household infection rates. These prior distributions will be used to generate posterior probabilities for the intervention arm.

#### Management of missing data

Information on why individuals chose not to participate or are lost to follow up will be collected. We anticipate few cases of missing data, assuming high adherence among participants and a low drop-out rate. However, to comply with the intent-to-treat analysis, all participants will be included in the data analysis. Hence, we will manage missing data using several strategies. First, if recorded data reports a change of outcome (e.g., change from positive to negative of a SARS-CoV-2 RT-PCR), we would carry forward that finding, as it is very unlikely that the result would change back to positive. Missing data where change has not occurred will be estimated using multiple imputation.

### Sample size and power considerations

Three hundred and ten households will be randomized to treatment or standard of care. Households will be randomized as clusters, assuming 4 individuals per household; approximately 1240 individuals will be enrolled. Data from Wuhan, China, suggest the proportion of untreated index cases still shedding virus at day 11 is ~ 85% [22]. A sample of 278 households (310 considering a 10% drop out rate) has > 90% power, at alpha 0.025, to detect a difference between the proportion of index cases shedding virus at day 11 between the treatment arm and standard of care arm, if the proportion is 65% in the treatment arm; based on a two-tailed Fisher’s exact test. In addition, the sample, including 834 household contacts (417 per arm), has > 90% power, at alpha 0.025, to detect an odds ratio of 0.5 for a reduction in transmission to a household contact; based on a two-tailed stratified Cochran-Mantel–Haenszel test, with intra-class correlation 0.15.

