### Primary and secondary objectives

The two co-primary objectives of this study are:To determine whether IFN ß-1a treatment reduces the proportion of infected cases shedding SARS-CoV-2 at day 11 after randomization.To determine whether IFN ß-1a treatment reduces the incidence of SARS-CoV-2 transmission from index cases to treatment-eligible household contacts, as measured by any positive upper airway infection evidenced by real-time Polymerase Chain Reaction (RT-PCR), in contacts at day 11 after randomization.

Secondary objectives of this study are:To determine whether in index cases infected with SARS-CoV-2, IFN ß-1a treatment compared with standard of care reduces the duration of SARS-CoV-2 upper airway virus shedding over 28 days following randomization.To determine whether IFN ß-1a treatment affects the incidence of SARS-CoV-2 upper airway infection or serological conversion by study day 29 in household contacts.To determine whether IFN ß-1a treatment compared with standard of care reduces the proportion of infected cases that require hospital admission or die due to COVID-19.To determine the safety of IFN ß-1a in the treatment and prevention of SARS-CoV-2 infection.

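### Each co-primary is powered at two-sided 0.025 and no step-down rule is stated; Holm would add a few points of power at the same 5% familywise error

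*Protocol article*

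**What the plan says.** Under Primary and secondary objectives the article states: "The two co-primary objectives of this study are" viral shedding in infected cases at day 11, and transmission to treatment-eligible household contacts by day 11. The Abstract's Discussion paragraph and the main Discussion treat these as two separate questions, each to be answered.

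Sample size and power considerations gives both objectives the same alpha.

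- Objective 1: the sample "has > 90% power, at alpha 0.025, to detect a difference between the proportion of index cases shedding virus at day 11". The test behind this figure is a two-sided Fisher's exact test.
- Objective 2: the sample "has > 90% power, at alpha 0.025, to detect an odds ratio of 0.5 for a reduction in transmission to a household contact". The test behind this figure is a two-sided Cochran-Mantel–Haenszel test with stratification, and the assumed within-household correlation is 0.15.

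These are the only two places where a significance level appears. The Data analyses section, including Secondary analyses, specifies regression models and 95% confidence intervals. It states no threshold for the primary tests, no decision rule and no multiplicity procedure, and it refers the detail to a statistical analysis plan that is available on request and was not seen here.

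**The concern.** Either objective can succeed on its own, so the pair needs control of the familywise error, and 0.025 each supplies it. Suppose the same 0.025 is then used as a fixed threshold in the final analysis. A p-value between 0.025 and 0.05 on one objective would count as a failure even when the other objective had clearly succeeded.

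Holm's procedure avoids this. It rejects everything the even split rejects. Once one objective has passed 0.025, it tests the other at 0.05. It keeps the familywise error at or below 5% whatever the correlation between the tests, which matters here because shedding by the index case and infection of contacts are plausibly related. What is at stake is power on the weaker objective and the chance of reporting both.

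**Working it through.** **Inputs.** From Sample size and power considerations: 85% shedding under control, 65% under treatment, 278 evaluable households, 834 contacts (417 per arm), intra-class correlation 0.15, odds ratio 0.5, two-sided 0.025 for each objective. Allocation is 1:1 (Treatment assignment and randomization), so 139 households per arm.

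**Step 1: reproduce the plan's figure for objective 1.** Exact enumeration of the two-sided Fisher test, 139 per arm, 85% against 65%:
- at 0.025: 93.9%, which agrees with the stated figure of more than 90%;
- at 0.05: 96.7%.

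**Step 2: error rate of the split.** 0.025 + 0.025 = 0.05; if independent, 1 − 0.975² = 0.0494. The split controls the 5% level. Under the global null, Holm rejects something exactly when the even split does. Its simulated familywise error was 5.0%, 4.8% and 4.5% at correlations 0, 0.3 and 0.6.

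**Step 3: objective 2 at the edge of the stated power.** Take exactly 90% at 0.025. The critical values are 2.241 (0.025) and 1.960 (0.05). The mean of the test statistic is 1.282 + 2.241 = 3.523, so power at 0.05 is Φ(3.523 − 1.960) = 94.1%.

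**Step 4: Holm against the even split, independent tests.** Under Holm an objective succeeds if it passes 0.025, or if it passes 0.05 and the other passes 0.025.

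- Objective 2: 0.900 + (0.941 − 0.900) × 0.939 = 0.938.
- Objective 1: 0.939 + (0.967 − 0.939) × 0.900 = 0.964.
- Both, even split: 0.939 × 0.900 = 0.845.
- Both, Holm: 0.845 plus the two gains above (0.025 and 0.038) = 0.908 to 0.909, depending on rounding, so about 91%.
- At least one, either method: 1 − (1 − 0.939) × (1 − 0.900) = 0.994. Unchanged, because Holm's first step is also at 0.025.

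**Step 5: sensitivity.** With correlation 0.3 and exactly 90% power on each objective, Holm gives about 93.3% on each, and the chance of both goes from 82.1% to 88.8%. With independent tests the same case gives 93.7% on each and 81.1% to 88.4% for both.

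The article does not state the control attack rate behind objective 2, so it is an assumption here. With a design effect of 1 + (3 − 1) × 0.15 = 1.3 there are 417 / 1.3 = 320.8 effective contacts per arm. Normal-approximation power at 0.025, and simulated Holm power with independent tests, are:

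| Assumed control attack rate | Objective 2 at 0.025 | Objective 2, Holm | Both, even split | Both, Holm |
|---|---|---|---|---|
| 10% | 50.7% | 61.2% | 47.7% | 59.4% |
| 20% | 80.8% | 87.2% | 76.0% | 84.5% |
| 25% | 88.2% | 92.6% | 82.9% | 89.6% |
| 30% | 92.6% | 95.6% | 87.0% | 92.5% |
| 40% | 96.7% | 98.2% | 90.9% | 94.9% |
| 50% | 98.1% | 99.0% | 92.1% | 95.7% |

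Only the rows from 30% upwards agree with the article's own claim of more than 90% power.

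**The case against.** The strongest objection is that the article never says the final tests are held at a fixed 0.025. The figure is a sizing input, and Holm also begins at 0.025, so a team planning Holm could have written exactly these power statements. The testing procedure is something an article commonly leaves to the statistical analysis plan, which may already name Holm. This stands. A reader might infer that the plan has committed to a fixed split and is giving up power, but the text supports only the conditional claim that it would do so if the split governs the final tests.

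Second, an even Bonferroni split is a legitimate, conservative method, and by the article's own account both objectives already exceed 90% power. This stands too: there is no error here.

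Third, the gain can be made to look larger than the documents allow. If objective 2 had only 70% power, Holm would lift the chance of showing both from 65.8% to 76.1%. No figure in the article gives 70%, and it contradicts the stated power. If power really were that low, the power statement would be the problem.

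Fourth, a fixed split has simple matching 97.5% confidence intervals, and Holm has no equally simple counterpart. That is true in general but carries little weight here, because the article plans 95% intervals and so does not use that advantage.

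**Conclusion.** The point holds as an optional improvement. If the implied even split is used for the final tests, Holm is uniformly more powerful at the same 5% familywise error and needs no additional patients or data. At objective 1 power of 93.9%, objective 2 power of 90% and independent tests, the gain is 2.5 points on objective 1 (to 96.4%), 3.8 points on objective 2 (to 93.8%) and about 6 points on showing both (84.5% to about 91%). At an assumed 30% attack rate the gain on both is about 5 points. At higher attack rates it is smaller, because objective 2 is then already better powered. There is no gain in the chance of at least one success.

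The size rests on the article's assumed effects, on independence (a correlation of 0.3 changes it little) and on objective 2 having about the stated power. A reader might go further and infer that the trial is wrongly designed or underpowered because of the split. The documents do not support that: the split controls the error rate, and the stated power for objective 1 reproduces.

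**What to change.** Unless the statistical analysis plan already contains such a rule, add one sentence to the analysis section before analysts are unblinded and the database is locked: the smaller of the two primary p-values is tested at two-sided 0.025 and, if it passes, the other is tested at two-sided 0.05; if the smaller does not pass, neither objective is claimed.

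Keep the sample size. Keep the 0.025 power figures and describe them as conservative minimums for each objective.

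The cost is that one sentence. It needs no extra households, samples or follow-up, and the familywise error stays at or below 5%.

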### Study population and inclusion/exclusion criteria

The study population will include individuals, between the ages 18 and < 80 years, who have tested positive for SARS-CoV-2 (RT-PCR) within the previous 72 h (Index Cases) and their household contacts (Eligible Contacts, between ages 18 and < 80 years, and Ineligible Contacts). Eligible households must include at least one eligible index case and one eligible household contact. Treatment ineligible participants will also be enrolled, to assess SARS-CoV-2 transmission within a household. Details of household and participant eligibility are proved in Fig. 2 and Table 1.

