### Biospecimen collection, processing, and storage

Peripheral blood, nasal samples and/or saliva will be collected from index cases and eligible household contact members at each study visit. Refer to Table 2. Samples will be taken by experienced staff, trained in the home visit procedures. All samples will be kept on ice and transported to the laboratory.

Each saliva sample will be collected by passive drool collection and spitting into a sterile container. Saliva samples intended for viral PCR will be collected in phosphate saline buffer (PBS) and kept on ice until final storage in the laboratory. Participants will be asked not to eat, smoke, drink or brush their teeth 30 min prior to the collection. Saliva collection will be followed by collection of nasal fluid samples using a synthetic absorptive device (Nasosorption FX, NSFL-FX-11 or NSFL-FXI-13), that absorbs the mucosal lining fluid. A second nasal sampling will consist of inserting an interdental brush into the nostril and gently twirling the brush against the inferior turbinate which runs along the lateral wall of the nasal passage. After collection, the brush is inserted into a sterile tube pre-filled with RNAlater (Life technologies cat# AM7021) to allow RNA stabilization until analysis. Blood samples are collected last, and a total of 23 ml of peripheral blood will be obtained from an easily accessible vein by experienced staff. A 21G butterfly needle will be used to draw blood into 3 distinct collection tubes; IVD PAXgene blood collection tube (BD, Cat. No. 762165) for RNA samples, CTP Vacutainer (BD, Cat. #362761) for mononuclear cells (PBMC) collection and Lithium Heparin vacutainers (BD, cat# 367526) for the remainder. At the end of collection, all biospecimens will be transported to the laboratory for further processing and/or storage.

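### The power for the transmission co-primary is computed on all 834 non-index household members, although that objective covers only treatment-eligible contacts

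*Protocol article*

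**What the plan says.** All references are to the protocol article.

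- *Sample size and power considerations*, on households: "A sample of 278 households (310 considering a 10% drop out rate) has > 90% power, at alpha 0.025". On household size and enrolment: "assuming 4 individuals per household; approximately 1240 individuals will be enrolled".
- Same section, on the second co-primary: "the sample, including 834 household contacts (417 per arm), has > 90% power, at alpha 0.025, to detect an odds ratio of 0.5". The test and clustering are given as "based on a two-tailed stratified Cochran-Mantel–Haenszel test, with intra-class correlation 0.15".
- *Analysis for primary objective 2* defines the outcome as "transmission from an index case to treatment-eligible household contacts". *Primary and secondary objectives* limits it in the same way.
- *Study population and inclusion/exclusion criteria*: "Treatment ineligible participants will also be enrolled, to assess SARS-CoV-2 transmission within a household". A household qualifies with one eligible index case and one eligible contact. Table 1 defines the ineligible group as people under 18, people aged 80 or over, and adults of 18 to under 80 with any listed contraindication.

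**The concern.** The contact count in the power statement and the population of the objective do not match. The count leaves no room for treatment-ineligible members, yet the protocol has a separate enrolment category for them, with parental consent and assent, and invites them at recruitment. Each such member among the assumed four takes one person out of the 834 for Objective 2.

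This is a co-primary objective. If its result is null, readers will weigh it against the stated power. A power figure computed on too large a sample makes such a result look more informative than it is.

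**Working it through.** **Inputs from the article.** 278 analysable households, 1:1, so 139 per arm; 4 people per household; odds ratio 0.5; two-sided alpha 0.025 (z = 2.241); intra-class correlation 0.15.

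**Inputs not in the article, so assumed over a range.** Mean number m of treatment-eligible contacts per household (3, 2.5, 2, 1.5); control attack rate p0.

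**Step 1: the contact count.** 278 × (4 − 1) = 834, and 834 / 2 = 417 per arm. Both match the article exactly. Enrolment also matches: 310 × 4 = 1240. So the four people per household are everyone enrolled, and 834 is everyone except the index case.

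**Step 2: check of the other co-primary.** With 139 per arm, 85% against 65% and alpha 0.025, exact Fisher power is 93.9%. That claim of more than 90% reproduces.

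**Step 3: formulas for Objective 2.**
- Design effect: DE = 1 + (m − 1) × 0.15
- Effective number per arm: n = 139 × m / DE
- Treated rate: p1 = 0.5·p0 / (1 − p0 + 0.5·p0)
- Power = Φ{ [(p0 − p1) − 2.241·√(2·p̄(1 − p̄)/n)] / √([p0(1 − p0) + p1(1 − p1)]/n) }, with p̄ = (p0 + p1)/2

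**Step 4: the article's own count (m = 3).** DE = 1 + 2 × 0.15 = 1.30; n = 417 / 1.30 = 320.8. At p0 = 27%, p1 = 15.6% and p̄ = 21.3%. The difference is 0.1139, the null standard error 0.0323 and the alternative standard error 0.0320. Power = Φ[(0.1139 − 2.241 × 0.0323) / 0.0320] = Φ(1.295) = 90.2%. The stated figure is thus reproduced conditionally, for a control rate of about 27% or more. Other versions of the test move this threshold little: 27.7% (Wald on the log odds ratio), 28.6% (continuity-corrected), between 28% and 29% (exact Fisher). Power falls below 90% again only above a control rate of about 85%.

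**Step 5: eligible contacts only.**

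| Mean eligible contacts (m) | Contacts per arm | DE | Effective n per arm | Power at p0 = 15% | 20% | 25% | 30% | 40% | p0 needed for 90% |
|---|---|---|---|---|---|---|---|---|---|
| 3 | 417 | 1.300 | 320.8 | 69% | 81% | 88% | 93% | 97% | about 27% |
| 2.5 | 347.5 | 1.225 | 283.7 | 63% | 75% | 84% | 89% | 94% | about 31% |
| 2 | 278 | 1.150 | 241.7 | 55% | 68% | 77% | 83% | 90% | about 39% |
| 1.5 | 208.5 | 1.075 | 194.0 | 45% | 57% | 66% | 73% | 82% | not reached (maximum 87.6%) |

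At p0 = 27%, where 834 contacts just give 90%, a mean of 2 eligible contacts gives 79.6%. The calculation assumes a common cluster size and no covariate adjustment; unequal cluster sizes would lower power somewhat.

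**The case against.** **The control rate may be in the full protocol or the analysis plan.** This stands. A condensed article may leave that input to those documents, and nothing in it contradicts a rate of 27% or more. A reader might take the missing rate as a defect in itself; it is not counted as one here. It matters only because the effect of the wrong count cannot be sized without it.

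**The claim of more than 90% may still be true.** This also stands. At a mean of 2.5 eligible contacts it holds from a control rate of about 31%, and at a mean of 2 from about 39%. A reader might infer that the trial is underpowered for transmission. The documents do not show that.

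**The mismatch may be loose labelling.** The power sentence speaks of "to detect an odds ratio of 0.5 for a reduction in transmission to a household contact" and does not say treatment-eligible. But the objective is defined as treatment-eligible in two places, so the power figure still describes a different population. If the four people meant one index case and three eligible contacts, ineligible members would come on top, enrolment would exceed 1240, and the enrolment figure would need correcting instead.

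**Ineligible members might be said to go unsampled.** *Biospecimen collection, processing, and storage* says specimens "will be collected from index cases and eligible household contact members at each study visit", which could be read that way. Their stated purpose, to assess transmission within the household, points to testing them, and Table 2 does not restrict saliva collection. The article is unclear on this, and the point does not depend on it: the definition of Objective 2 already leaves them out.

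**It is late to restate power.** With 251 of 310 households enrolled, a new figure changes neither the analysis nor the confidence interval. That limits the consequence but does not make the printed count right.

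**Conclusion.** The point holds as a mismatch of populations. Under the article's four-person assumption, 834 is the largest possible number of contacts for Objective 2. It is reached only if no household includes a child, a person aged 80 or over, or an adult contact with a contraindication. The direction is certain: any ineligible member lowers the count, and power is then below what 834 contacts would give. The size is not known. Across means of 3 down to 2 eligible contacts, the control rate needed for 90% power rises from about 27% to about 39%; at 1.5 no control rate suffices. These figures rest on assumed eligible-contact means and control rates, combined with the article's alpha, odds ratio, intra-class correlation and number of households. They support saying that power is lower than the 834-based figure and may fall below 90%, and no more than that.

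**What to change.** In *Sample size and power considerations*, replace 834 (417 per arm) with the expected number of treatment-eligible contacts in 278 households, using the mean observed in the 251 households already enrolled. For that number, restate power at an odds ratio of 0.5, or give the odds ratio detectable with 90% power, and name the control attack rate used. Keep the population as the analysis section defines it: that analysis adjusts for the contacts' baseline RT-PCR result, so the restated figure should not bring in a restriction to baseline-negative contacts.

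The cost is a revised paragraph and probably a less favourable stated power. No added participants and no change to the analysis are needed.
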